# Abstract

ICSI is commonly used in PGT cases to eliminate any risk of sperm DNA contamination. With the switch from cleavage stage biopsy to biopsy of the full (hatching) blastocyst, this potential risk of contamination can be neglected and could allow the use of conventional IVF in PGT cases. Especially in cases of non-male factor infertility, the use of conventional IVF can be applied as a more ‘natural’ insemination method.

A pilot study will be performed on sibling oocytes including patients with non-male factor infertility and requesting PGT-A (NGS platform). If at least 10 cumulus oocyte complexes (COCs) are obtained after oocyte retrieval, half of the oocytes will be subjected to ICSI and the other half to conventional IVF. Preimplantation development is followed by time lapse imaging and blastocysts (day 5-7) fulfilling the biopsy criteria will undergo trophectoderm biopsy to detect the ploidy state and the mtDNA copy number.

The main objective is to analyse if the use a more physiological insemination method (IVF) has a beneficial impact on the ploidy state of the blastocyst as compared to ICSI within the same patient. As the embryos will be cultured in a time lapse imaging system, annotations can be made and the differences in maturation rate, fertilization rate and embryo development between both insemination methods can be analysed as secondary outcome parameter. On top of this, the PGT-A outcome will also display the mtDNA copy number which can be compared between IVF and ICSI biopsied sibling blastocyst. Euploid blastocysts will be transferred in subsequent FET cycles and give an indication on the clinical outcome between IVF and ICSI.

Would this study enable us to undermine the dogma to perform ICSI for all PGT cycles?

# List of acronyms

| ICSI | Intracytoplasmic sperm injection |
| --- | --- |
| AMH | Anti-Müllarian Hormone |
| ASRM | American Society for Reproductive Medicine |
| BL | Blastocyst |
| BMI | Body Mass Index |
| aCGH | Array Comparative Genomic Hybridization |
| CLBR | Clinical Live Birth Rate |
| COC | Cumulus Oocyte Complex |
| DNA | Deoxyribonucleic acid |
| mtDNA | Mitochondrial Deoxyribonucleic acid |
| E_2_ | Estrogen |
| FET | Frozen Embryo Transfer |
| β-hCG | β chain of the human chorionic gonadotropin |
| hCG | Human chorionic gonadotropin |
| ESHRE | European Society of Human Reproduction and Embryology |
| IC | Informed Consent |
| ICM | Inner Cell Mass |
| IF | Impact Factor |
| IVF | In vitro fertilization |
| IU | Internal Units |
| kg/m^2^ | Kilogram per length^2^ |
| ml | milliliter |
| ng/ml | Nanogram per milliliter |
| NA | Not Applicable |
| NGS | Next Generation Sequencing |
| NP | Non-progressive motile sperm |
| OPU | Oocyte Pick-Up |
| P | Progesterone |
| pg/ml | Pictogram per milliliter |
| PGT | Preimplantation Genetic Testing |
| PGT-A | Preimplantation Genetic Testing for Aneuploidies |
| PGT-M | Preimplantation Genetic Testing for Monogenic Disorders |
| PN | Pronuclei |
| PR | Progressive Motile Sperm |
| SOP | Standard Operating Procedure |
| SIVIS | Software for medical record management |
| TE | Trophectoderm |
| UAE | United Arab Emirates |
| USA | United States of America |
| WHO | World Health Organization |
|  |  |

# AIM: main objective/research question

The primary aim is to verify if the insemination method (IVF or ICSI) on sibling oocytes influences the ploidy state of the blastocyst, as tested by PGT-A.

# Secondary Objectives/research questions

1. Pre-implantation development parameters between both insemination methods (IVF or ICSI) defined by:

- Maturation rate: number of mature oocytes obtained in each arm
  - ICSI: defined on day 0 as the number of injected oocytes/number of COCs assigned to the ICSI group
  - IVF: defined on day 1 as the number of oocytes with an extruded PB/number of inseminated oocytes
- Fertilization rate: number of zygotes with 2PN/number of oocytes assigned to the group
- Embryo quality on day 3 defined by the Istanbul consensus (Alpha Scientists, 2011)
  - The number of blastomeres and their division pattern, fragmentation, presence of compaction, vacuoles, granulation and nuclei will divide the embryos into 3 categories: good, fair or poor
  - Cell number on day 3 for all fertilized oocytes
- Embryo quality on day 5 (Gardner and Schoolcraft,1999) defined by the Istanbul consensus (Alpha Scientists, 2011)
  - The blastulation rate: number of embryos reaching at least the BL1 stage/ number of oocytes assigned to that group: defined by a 1 (yes, the embryo is blastulating) or 0 (no, the embryo is not blastulating)
  - The expansion stage of the blastocyst and the quality of the ICM and TE will divide the embryos into 3 categories
- Utilization rate: number of embryos that can be used for the patient (=number of embryos that can be biopsied)/number of oocytes assigned to the group
- Morphokinetic parameters defined by time lapse imaging starting from the time of syngamy (Basile et al., 2014)
- Morphokinetc parameters and their effect on ploidy, day of biopsy, biopsy or not and gender

1. mtDNA (de los Santos et al., 2018) per cycle and between IVF or ICSI generated embryos:

- Mitoscore value: represents the normalized mtDNA content in (an)euploid embryos and indicates the total mtDNA content in the sample

1. Cycle outcome defined by (Zegers-Hochschild et al., 2017) per cycle and also per insemination method (IVF or ICSI):

- Pregnancy (yes or no) defined by a βhCG test of > 15IU
- Biochemical pregnancy (yes or no) defined as a pregnancy in which the hCG levels start do decrease after 1 week
- Implantation rate (%) defined by the number of gestational sacs/number of embryos transferred
- Clinical pregnancy (yes or no) defined by the ultrasonographic visualization of one or more gestational sacs, including ectopic pregnancies.

# Introduction

## Background:

In case of non-male factor infertility, IVF should be chosen as insemination method. However, in Europe and the USA, 65-75% of all IVF cycles use ICSI as insemination method (Dyer et al., 2016; Boulet et al., 2015) even though there is no clear evidence why a couple would benefit from ICSI over conventional IVF as the CLBR is not different between IVF and ICSI cycles (Li et al., 2018). As many fertility clinics prefer the use of ICSI to maximize the fertilization rate, the cleavage and blastocyst formation rate is comparable when sibling oocytes are inseminated with conventional IVF or ICSI (Van Landuyt et al., 2005). Besides these static parameters, the dynamic morphokinetic parameters between such siblings have not yet been described.

If PGT is to be applied, ICSI has always been the method of choice, especially for day 3 cleavage embryos. The choice of ICSI over IVF comes from the idea that contamination of residual sperm DNA has to be prevented. With the switch of embryo biopsy from day 3 to the full (hatching) blastocyst on day 5/6, this contamination can be completely eliminated. From this viewpoint it would be interesting to analyse the ploidy outcome (PGT-A) in IVF versus ICSI cycles after trophectoderm biopsy. A similar study has been performed with the use of PGT-M on day 3 embryos (Feldman et al., 2017). Conventional IVF-only cycles, ICSI-only cycles and IVF/ICSI mixed cycles were included and it was concluded that IVF can perfectly be applied for PGT-M with a negligible rate of sperm contamination. Similarly, a study analysing IVF or ICSI blastomeres with FISH (7 probes) was unable to detect differences in aneuploidy rate between both insemination methods (Şahin et al., 2017). However, this use of IVF/ICSI sibling oocytes has never been performed for day 5-7 PGT-A analysis.

Interestingly the mtDNA copy number is also analysed in PGT-A cycles; as trophectoderm quality and ploidy state have been described to affect the mtDNA copy number in ICSI cycles, the question remains whether this is also influenced by the insemination method.

This leaves the question if the use a of more physiological insemination method (IVF) has a beneficial impact on the ploidy state, embryo development and mtDNA content as compared to ICSI.

## Justification:

To the best of our knowledge, no study has been performed analysing the ploidy state and mtDNA content by PGT-A on IVF/ICSI sibling embryos. Also, no studies are available comparing the developmental kinetics by time lapse imaging between IVF and ICSI embryos within the same patient.

With the overuse of ICSI for non-male factor infertility, this study aims to provide evidence that conventional IVF should be the method of choice.

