## Sample Size

Considering no study has been performed analyzing the ploidy state, mtDNA content and embryo morphokinetics by PGT-A on IVF/ICSI sibling embryos, we propose a pilot study including 30 couples to assess the feasibility of the study. Moreover, the pilot study will allow us to estimate statistical parameters which enables us to calculate a sample size in a future study in which an acceptable level of power can be established.

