### Objectives assessment

Main objective

In order to compare the effect of IVF versus ICSI on the blastocyst ploidy state a Poisson regression will be performed, which is the most appropriate statistical modelling method to analyse count data.

Secondary objectives

To compare IVF versus ICSI outcomes in preimplantation development outcomes:

- To compare the maturation rate, a t-test will be used to detect differences in the average number of mature oocytes (a Wilcoxon test will be used if we cannot assume normal distribution of data). If we found differences, linear or Poisson regressions will be performed to evaluate them in a model taking into account rest of explanatory variables.
- To compare the fertilization rate, a t-test will be used to detect differences in the average number of zygotes with 2PN oocytes (a Wilcoxon test will be used if we cannot assume normal distribution of data). If we found differences, linear or Poisson regression will be performed to evaluate them in a model taking into account rest of explanatory variables.
- In order to compare embryo quality on D3 (measured using the Istanbul consensus), a multinomial logistic regression will be performed.
- Embryo quality D5
  - To compare the blastulation rate, a t-test will be used to detect differences in the average number of embryos reaching at least the BL1 stage (a Wilcoxon test will be used if we cannot assume normal distribution of data). If we found differences, linear or Poisson regressions will be performed to evaluate them in a model taking into account rest of explanatory variables.
  - In order to compare embryo quality on D5 (The expansion stage of the blastocyst and the quality of the ICM and TE will divide the embryos into 3 categories), a multinomial logistic regression will be performed.
- To compare the utilization rate, a t-test will be used to detect differences in the number of embryos that can be used for the patient (a Wilcoxon test will be used if we cannot assume normal distribution of data). If we found differences, linear or Poisson regressions will be performed to evaluate them in a model taking into account rest of explanatory variables.

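### The Justification promises evidence that IVF should be the method of choice, but the study is a 30-couple feasibility pilot that cannot support such a conclusion

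*Protocol*

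**What the plan says.** The Protocol describes the purpose of the study in several ways.

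- **AIM section:** a neutral question. "The primary aim is to verify if the insemination method (IVF or ICSI) on sibling oocytes influences the ploidy state of the blastocyst".
- **Abstract, main objective:** a question of benefit, namely whether IVF "has a beneficial impact on the ploidy state of the blastocyst as compared to ICSI within the same patient".
- **Abstract, last line:** a question about practice. "Would this study enable us to undermine the dogma to perform ICSI for all PGT cycles"?
- **Introduction, Justification:** a conclusion named in advance. "this study aims to provide evidence that conventional IVF should be the method of choice".
- **Sample Size:** a pilot. "we propose a pilot study including 30 couples to assess the feasibility of the study". Its estimates are meant to feed "a future study in which an acceptable level of power can be established".
- **Objectives assessment, main objective:** one planned comparison. "In order to compare the effect of IVF versus ICSI on the blastocyst ploidy state a Poisson regression will be performed".

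The Background section cites work in which the two methods did not differ. One example is a seven-probe FISH study of blastomeres that "was unable to detect differences in aneuploidy rate between both insemination methods". It then notes that the sibling-oocyte design has not yet been used for PGT-A on day 5-7 blastocysts.

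**The concern.** The Justification commits the study to a recommendation on practice in one direction. The Sample Size section says that the study has no established power and exists to plan another one. Both cannot describe the same 30 couples.

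What is at stake is how the likeliest result will be reported. With this few couples, a non-significant ploidy comparison is likely both when the methods are equal and when IVF yields moderately fewer euploid blastocysts. The Background already leans on findings of no difference when it argues against routine ICSI, and the Justification names the conclusion before any data exist. Nothing in the text stops a null result from being cited for IVF, although such a result would not show that a loss of about 10 percentage points is absent.

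**Working it through.** **Nothing to reproduce.** The figure of 30 couples is given as a feasibility number, with no effect size, euploidy rate, significance level or power behind it. The check therefore asks what a non-significant result from 30 couples could exclude.

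**Inputs from the Protocol:** 30 couples; at least 10 oocyte complexes per couple, split in half, so about 5 or more per arm; outcome per blastocyst euploid or aneuploid.

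**Assumptions not in the Protocol:** 1.5 to 5 biopsied blastocysts per arm per couple, so n = 30 × 1.5 = 45 to 30 × 5 = 150 per arm; euploidy with ICSI p1 = 50%; two-sided 5% test; blastocysts independent. With a true loss d, p2 = p1 − d and p̄ = (p1 + p2)/2.

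**Chance of missing the loss:**

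miss = Φ{[1.96 √(2p̄(1−p̄)/n) − d] / √(p1(1−p1)/n + p2(1−p2)/n)}

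Example with n = 60 and d = 0.10: p̄ = 0.45; 1.96 × √(0.495/60) = 0.178; √(0.49/60) = 0.0904; (0.178 − 0.100)/0.0904 = 0.863; Φ(0.863) = 0.806.

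**Half-width of the 95% CI** at 50% in both arms: 1.96 √(0.5/n).

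| n per arm | 10-point loss missed | 15-point loss missed | 20-point loss missed | CI half-width (points) |
|---|---|---|---|---|
| 45 | 84% | 70% | 51% | 20.7 |
| 60 | 81% | 62% | 39% | 17.9 |
| 90 | 73% | 47% | 21% | 14.6 |
| 120 | 66% | 35% | 11% | 12.7 |
| 150 | 59% | 25% | 5% | 11.3 |

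**Sensitivity to the euploidy rate.** With ICSI euploidy of 40-60% instead of 50%, the ranges become 56-84%, 21-71% and 3-53%.

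**Sensitivity to couples.** A simulation gave each couple its own euploidy level (assumed SD 0.8 on the logit scale) and 1.5 to 4 blastocysts per arm. A couple-stratified test missed the three losses 66-87%, 34-75% and 12-63% of the time. A test on total euploid counts missed them 79-90%, 57-80% and 31-68% of the time. The independence assumption does not drive the result.

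**If the methods are truly equal.** The chance that the lower 95% limit excludes a 10-point loss is Φ(0.10/√(0.5/n) − 1.96). This is Φ(1.095 − 1.96) = 19% at n = 60 and Φ(1.549 − 1.96) = 34% at n = 120, that is, at 2 to 4 blastocysts per arm per couple. For 80% power to exclude a 10-point loss, 393 blastocysts per arm are needed, or about 99 (393/4) to 197 (393/2) couples before any allowance for pairing or clustering. The 10 points are an illustration; the Protocol gives no margin.

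**The case against.** The sentence on the method of choice stands in a motivational section. The formal aim is neutral and the Abstract's main objective asks about benefit; a test for a difference suits both, and neither needs a non-inferiority margin. The closing line of the Abstract is a question. The usual reason for ICSI in PGT is sperm DNA contamination, so challenging that habit is not in itself a claim about euploidy. The document openly calls itself a pilot and defers power, so the miss rates put numbers on a disclosed limitation. Significance level, sidedness and rules of interpretation are commonly left to a SAP, which is not at hand here.

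Most of this stands. Thirty couples is no error for a pilot, and the absence of a margin, a significance level or a stated interval is not the point. What remains is that the Justification goes beyond the formal aim to a recommendation that the Sample Size section says the study is not sized to support. A SAP could add rules of analysis but would not remove that aim from the Protocol. Nor would reading the question as superiority help: at 50% euploidy, a true 10-point gain with IVF is missed as often as a 10-point loss.

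Two stronger readings are tempting. A reader might infer that the investigators plan to count a non-significant result as support for IVF. No section says so, and the Background treats the question for day 5-7 blastocysts as still open. A reader might also infer that any real loss would almost certainly be missed. The table does not bear this out: losses of 15 to 20 points are often detected when blastocysts are numerous.

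**Conclusion.** The point holds as a conflict between stated purpose and design. The Justification claims more than a 30-couple feasibility pilot with a single ploidy comparison can deliver, and it leaves room to cite a null result for IVF.

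A non-significant result could not rule out a 10-point loss of euploidy, which would be missed about 59-84% of the time. For 15 points the range is about 25-70%, and for 20 points about 5-51%. All these figures rest on an assumed 50% euploidy with ICSI, 45-150 biopsied blastocysts per arm, a two-sided 5% level and independent blastocysts. The Protocol gives none of them, so the ranges should be read as conditional. The conflict itself does not depend on them.

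**What to change.** 1. **Justification, and the last line of the Abstract:** limit the aim to estimating the IVF-ICSI difference in blastocyst euploidy in order to plan a confirmatory study. State that this pilot will not establish IVF as the method of choice.
2. **Objectives assessment, main objective:** make the within-couple IVF minus ICSI difference in euploid proportion, with a 95% CI that accounts for clustering by couple, the primary result. State that a non-significant comparison is neither evidence of equivalence nor support for replacing ICSI.
3. **Sample Size:** leave any non-inferiority margin, and any method-of-choice claim, to the future powered study. The pilot's estimate and interval can feed its sample-size calculation.

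The cost is wording and one interval, with no extra couples, procedures or staff. The small downside is that the pilot's paper can claim less.

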# Methodology

## Study Design

A pilot study will be performed on sibling oocytes comparing the effect of two insemination methods (IVF versus ICSI) on the blastocyst ploidy state.

## Study period and context

The study will start after protocol approval, and approval from the ethical committee, estimated in October 2018. Patients performing a fertility treatment at IVI Middle East Fertility Clinic, Abu Dhabi can be included if they accept to participate in the study and after signing the informed consent. It is estimated that all patients can be included in a period of three months.

Pre-implantation development, mtDNA copy number and PGT-A will be analyzed. All the aforementioned data collected for this study is obtained by usual practice.

## Reference Population

The study population is defined by all couples seeking a fertility treatment due to primary or secondary infertility in IVI RMA Abu Dhabi, for non-male factor infertility in combination with a PGT-A request.

## Subject Inclusion/exclusion criteria

*Inclusion criteria*

- Sperm parameters
  - Sperm concentration before capacitation: >15*10^6^ per ml (WHO)
    - Total motility (PR+NP,%): >40 (WHO)
    - Progressive motility (PR,%):>32 (WHO)
  - Sperm concentration after capacitation: >0.6*10^6^ per ml (not WHO defined)
    - Progressive motility (PR,%):>65 (WHO)
- ≥10 COCs after oocyte retrieval
- BMI ≤30 kg/m^2^
- Female age 18 to ≤ 40 years
- All ovarian stimulation protocols
- Fresh ejaculates
- Presence or absence of sperm morphology data: as we do not have a diagnostic sperm analysis for all patients, the presence or absence of >4% normal morphology (WHO) will not be taken into account, even with known low (<4%) normal morphology
- Couples requesting PGT-A
- Arab population

*Exclusion criteria*

- If after denudation (ICSI) only 2 mature oocytes are obtained
- If all time lapse spaces are occupied
- If the volume to be added after IVF is insufficient to perform IVF on all needed oocytes
- Presence of >1 *10^6^ per ml round cells in the ejaculate
- If a couple’s previous cycle was included in the study

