## Intervention and Follow-up

Couples that are eligible for the study will be selected on the day of OPU based on all inclusion and exclusion criteria (as described under “D. Subject inclusion/exclusion criteria”) and will be asked to participate in the study by signing the IC. A randomization list will determine to which group the first half (or one extra in case an odd number is available) of the oocytes will be assigned. As to prevent selection bias, oocytes will be assigned to both groups under low magnification and different cumulus expansion stages will be evenly divided. Oocytes selected for ICSI will be denuded and injected on the day of OPU after which their pre-implantation development will be followed by time lapse imaging. IVF oocytes will be inseminated (individual or per two) overnight with 10.000 PR sperm cells in a G185 incubator (K systems) and denuded in the morning of day 1 after which they will be transferred to the time lapse imaging incubator. Blastocysts of sufficient quality (to determine this, morphokinetic parameters shall be measured) will be biopsied on day 5-7 after which the blastocysts are vitrified individually. PGT-A (NGS platform) is performed on all TE biopsy samples and the ploidy state and mtDNA score will be provided. All annotated time lapse imaging data will be gathered and combined with the pre-implantation data, PGT-A data (ploidy state and mtDNA copy number) and all general patient and cycle characteristics. Patients with euploid embryos available will receive a FET and implantation rates and (clinical) pregnancy outcomes will be recorded.

The follow-up of the patients does not deviate from a normal fertility trajectory.

Quantification of the determining variables:

The primary outcome variable is the ploidy state

Secondary outcome variables are the (i) embryo development defined by the number of COCs retrieved, maturation and fertilization rate, embryo development analysed on day 3 and day 5, total number of embryos used for the patient, day of biopsy and the morphokinetic parameters; (ii) mtDNA copy number and (iii) the clinical outcome.

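### Couples can be excluded after oocyte allocation on the ICSI half's maturity alone, which tilts the secondary per-assigned-oocyte rates towards ICSI

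*Protocol*

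**What the plan says.** Under Subject Inclusion/exclusion criteria, a couple enters with "≥10 COCs after oocyte retrieval" and is excluded "If after denudation (ICSI) only 2 mature oocytes are obtained".

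Intervention and Follow-up gives the order of events. Couples "will be selected on the day of OPU based on all inclusion and exclusion criteria" and are then asked for consent. The split comes next: "A randomization list will determine to which group the first half (or one extra in case an odd number is available) of the oocytes will" go. After that, "Oocytes selected for ICSI will be denuded and injected on the day of OPU", whereas the IVF oocytes are inseminated overnight and "denuded in the morning of day 1 after which they will be transferred to the time lapse imaging incubator".

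Maturation rate is a secondary outcome. For one arm it reads "ICSI: defined on day 0 as the number of injected oocytes/number of COCs assigned to the ICSI group"; for the other it is counted on day 1 per inseminated oocyte. Fertilization, blastulation and utilization rates all take the oocytes assigned to the group as denominator. Statistical data analysis compares average numbers per arm for these outcomes. For the primary outcome it names a Poisson regression for counts and states no denominator.

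**The concern.** The maturity criterion cannot be applied when the Protocol says eligibility is settled. It needs a result that appears only after the split, and only in one half. A couple whose ICSI half happens to mature poorly leaves; a couple whose IVF half matures equally poorly stays. The retained ICSI halves are thus a favourably selected set, while the retained IVF halves are not selected on their own result.

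The trigger is the numerator of the ICSI maturation rate, so that outcome is affected most directly. Every other rate per assigned oocyte inherits the effect, because an immature oocyte cannot add to its numerator. The Sample Size section says the pilot is to supply parameters for a later trial, so a selected sample would carry its bias forward. Unless the excluded couples are recorded, it cannot be undone afterwards.

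**Working it through.** **Inputs from the Protocol.** At least 10 COCs, so at least m = 5 per half; 1:1 split within couple; trigger on the ICSI half only; 30 couples planned. There is no stated figure to reproduce, because the Protocol gives no calculation on this point.

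**Assumptions, not in the Protocol.** Maturity probability p, equal in both arms (no true difference), shown from 0.6 to 0.9; the number of COCs per couple; oocytes independent within a couple, relaxed below. The rule is read as 2 or fewer.

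**Formula.** Let X ~ Binomial(m, p) be the number of mature ICSI oocytes. Couples lost: P(X ≤ 2). Retained ICSI maturation rate: E[X | X > 2]/m = (mp − E[X; X ≤ 2]) / (m·P(X > 2)). With independence, IVF stays at p.

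**Worked case, m = 5, p = 0.75.**
- P(0) = 0.00098, P(1) = 0.01465, P(2) = 0.08789. Sum = 0.1035, so 10.4% of such couples are lost.
- E[X; X ≤ 2] = 1 × 0.01465 + 2 × 0.08789 = 0.1904.
- E[X | X > 2] = (3.75 − 0.1904)/0.8965 = 3.971, and 3.971/5 = 79.4%.
- Gap = 79.4 − 75.0 = +4.4 points; ratio = 3.971/3.75 = 1.06.

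**Spurious ICSI minus IVF maturation, percentage points.**

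| COCs per half | p = 0.60 | 0.70 | 0.75 | 0.80 | 0.90 |
|---|---|---|---|---|---|
| 5 | +12.2 | +6.6 | +4.4 | +2.6 | +0.4 |
| 6 | +6.7 | +3.0 | +1.7 | +0.8 | +0.1 |
| 7 | +3.7 | +1.3 | +0.6 | +0.3 | 0.0 |
| 8 | +2.0 | +0.5 | +0.2 | +0.1 | 0.0 |

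At 5 per half, the couples lost are 31.7, 16.3, 10.4, 5.8 and 0.9% across the same values of p.

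**Averaged over eligible couples.** With COCs assumed uniform from 10 to 20 and p = 0.75, 2.4% of couples are lost (30 × 0.024 = 0.7 couples). The gap is +1.0 point as a mean of couple-level rates, or +0.8 pooled over oocytes. At p = 0.70 the pooled gap is +1.3.

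**Between-couple variation.** With p varying between couples as a beta distribution (mean 0.75, SD 0.15) and 5 per half, 15.4% are lost. Retained ICSI is 82.7% against 78.2% for IVF, a gap of +4.5. Both arms rise, because poor-maturity couples leave, but the one-sided gap remains.

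**Exactly 2 instead of 2 or fewer, 5 per half.** +6.0, +4.6, +3.4, +2.2 and +0.4 points across the same p. The direction is unchanged over this range.

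**Downstream rates.** If each mature oocyte fertilizes with the same probability f whatever the count, 2PN per assigned oocyte is f times maturity. The ratio of 1.06 then carries over to fertilization and, by the same argument, to blastulation and utilization. It would also carry over to a count of euploid blastocysts modelled without a denominator.

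**Without the exclusion.** Both halves have expectation mp, so the expected gap is 0.

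**The case against.** The strongest objection is about reach. The primary outcome is blastocyst ploidy, and the number of mature oocytes does not by itself change the chance that a given biopsied blastocyst is euploid. This stands. A reader might infer that the primary comparison is biased. The Protocol supports that only if the Poisson model counts euploid blastocysts with no denominator, which it leaves open.

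Second, +4.4 points belongs to couples at the entry threshold of 10 COCs, and the gap shrinks quickly above it. This stands too. For scale, with 30 couples at 5 COCs per half and p = 0.75, the binomial standard error of the arm difference is √(2 × 0.75 × 0.25/150) = 5 points, so even the threshold case lies below one standard error. A bias, however, does not shrink as couples are added.

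Third, a reader might say the rule breaks the sibling randomisation. That is too strong: both halves of a couple leave together and the pairing is kept. The distortion is in mature-oocyte yield and what follows from it.

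Fourth, a reader might see the same fault in the IVF-side criterion, "If the volume to be added after IVF is insufficient to perform IVF on all needed oocytes". Intervention and Follow-up places eligibility before consent and the list. Sperm volume, unlike maturity after denudation, can be checked then; it is not an oocyte result, and no direction of bias follows from it.

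Fifth, taken literally the wording would exclude a couple with 2 mature oocytes and keep one with 0 or 1. No more than 2 is the natural reading, and nothing here depends on the literal one.

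**Conclusion.** The point holds for the maturity criterion and for the secondary outcomes counted per assigned oocyte. The criterion acts after allocation, on one arm's result, and contradicts the Protocol's own order of eligibility, consent and allocation. The bias favours ICSI in every case computed. Its size depends on a maturity rate and a COC distribution that the Protocol does not give. At an assumed 75% maturity it is +4.4 points at the minimum of 5 COCs per half (+2.6 at 80%, +6.6 at 70%), falls to +0.2 at 8 per half, and averages about +1 point if COCs spread evenly from 10 to 20. The euploid proportion per biopsied blastocyst and the Mitoscore are not directly affected. Should-fix.

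**What to change.** Change the analysis set, not patient care:

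- Stop using this criterion to remove couples from the analysis. Analyse every couple whose COCs were split, in the halves as allocated, with the observed number of mature ICSI oocytes (0, 1 or 2 included).
- Report how many couples meet the rule. Show results without them only as a sensitivity analysis.
- Reconcile the exclusion list with Intervention and Follow-up on when the criterion applies. The Protocol does not say how the IVF half of such a couple is handled; it should say so, so that readers know which IVF data exist.

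The cost is a short amendment. A few couples with little ICSI information stay in the data set.
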